## Abstract

**Background:**

The purpose of this clinical study is to investigate the clinical feasibility and effectiveness of offline Positron-Emission-Tomography (PET) quality assurance for promoting the accuracy of proton and carbon ion beam therapy.

**Methods/Design:**

A total of 240 patients will be recruited, evenly sampled among different analysis groups including tumors of the brain, skull base, head and neck region, upper gastrointestinal tract including the liver, lower gastrointestinal tract, prostate and pelvic region. From the comparison of the measured activity with the planned dose and its corresponding simulated activity distribution, conclusions on the delivered treatment will be inferred and, in case of significant deviations, correction strategies will be elaborated.

**Discussion:**

The investigated patients are expected to benefit from this study, since in case of detected deviations between planned and actual treatment delivery a proper intervention (e.g., correction) could be performed in a subsequent irradiation fraction. In this way, an overall better treatment could be achieved than without any in-vivo verification. Moreover, site-specific patient-population information on the precision of the ion range at HIT might enable improvement of the CT-range calibration curve as well as safe reduction of the treatment margins to promote enhanced treatment plan conformality and dose escalation for full clinical exploitation of the promises of ion beam therapy.

**Trial Registration:**

NCT01528670

## Background

In comparison to conventional external beam radiotherapy with photon and electron radiation, ion therapy may offer superior conformation of the dose delivery to the tumour, with improved sparing of the surrounding healthy tissue and critical organs. This is mainly due to the favourable energy deposition, which can be concentrated in a few millimeters narrow region (the Bragg-peak) at an adjustable depth [1]. However, exploitation of this selectivity to its full extent in the clinical practice is still hampered by uncertainties in the knowledge of the beam range in the patient, resulting in the usage of generous safety margins as well as avoidance of beam portals stopping directly in front of critical organs. In fact, the complete stopping of the primary ion beam in the patient prevents the applicability of conventional quality assurance techniques like electronic portal imaging [2], which are well established in clinical radiotherapy practice with photon radiation. Hence, treatment planning algorithms can only be based on models and data which are accurately validated in tissue-equivalent phantoms [3,4], but no direct in-vivo verification within the patient is currently feasible.

Nowadays, Positron-Emission-Tomography (PET) offers the only technically feasible method for an indirect three-dimensional (3D), in-vivo, non-invasive verification of ion treatment during or shortly after irradiation [5-11]. The method is based on the detection of the transient β^+^-activity which is formed as a by-product of the therapeutic irradiation (i.e., without administering any radio-tracer to the patient) in nuclear reactions between the incoming ions and the target nuclei of the irradiated tissue. By correlating the measured activity with the planned treatment and the actual patient anatomy as given by a computed tomogram (CT), it is possible to infer valuable information on the actual dose delivery. As activity and dose are different physical quantities, an additional comparison of the acquired PET images with a corresponding activation pattern deduced from the planned treatment and the specific time course of irradiation and imaging is strongly recommended [6,11]. This expectation can be obtained from a detailed Monte Carlo calculation of the ion beam transport and interaction within the patient [6,12-14], combined with the estimation of the fraction of activity carried away from the place of production by physiological processes such as perfusion, generally referred to as "biological washout" [6].

The technical implementation of PET monitoring can be performed using dedicated (typically limited angle) instrumentation directly located at the treatment site for in-beam [11] or in-room [8] acquisition, or using commercial nuclear medicine PET and PET/CT scanners installed closeby to the treatment unit for offline imaging [6,7,9,10]. In all cases, up-to-date anatomical information of the patient can be obtained from control CTs (cone-beam or full-ring scanner) which are acquired in regular intervals as a standard of care to evaluate correct patient positioning or to detect any anatomical changes during the course of the fractionated treatment in particle therapy. Therefore, no additional CT-imaging is required for correlation with PET measurements; however, when an additional CT is available, anatomical changes may be monitored and detected.

Promising experience in PET imaging of proton and carbon ion therapy has been so far obtained for more than 50 patients monitored after passive proton treatments in USA and Japan, as well as more than 400 patients monitored during scanned carbon ion beam irradiation at GSI Darmstadt, Germany [5-11]. In particular, the GSI pilot project demonstrated the value of PET for improving the accuracy of the semi-empirical CT-range calibration curve employed by the treatment planning system as well as for detecting and quantifying deviations between planned and actual treatment delivery due to patient misalignments or anatomical changes over the course of fractionated therapy [5,11,15]. Therefore, this clinical experience clearly indicates the potential value of the method especially in the starting phase of a new facility such as the Heidelberger Ionenstrahl Therapiezentrum (HIT) [16]. For this purpose, a commercial PET/CT scanner has been installed at HIT in a dedicated room closeby to the treatment area. However, the results from different therapy facilities cannot be directly translated to the HIT center due to the differences in the clinical protocol (fraction dose, number of portals), ion species (p,^12^C), beam-delivery system (passive scattering or active pencil-beam scanning), detector properties (full-ring or limited angle PET scanner, detection technology), imaging protocol (in-beam, in-room or off-beam data acquisition [17]), as well as the limited number of the so far investigated tumor types and sites. Therefore, a pilot clinical study is needed at HIT in order to identify the patient population which may benefit from PET imaging, as well as extract population-based information on the reliability of the delivered beam range for the available ion species in different tumour locations.

In the proposed clinical study MIRANDA (**M**on**i**toring of Patients t**r**eated with P**a**rticle Therapy using Positro**n**-Emission-Tomography) patient selection will be particularly addressed to those more crucial situations where utmost precision in the delivery of the planned dose with optimal sparing of the surrounding critical structures is mandatory. Especially in those cases where the ions have to penetrate highly inhomogeneous tissue, the precision of the intended dose deposition can be severely undermined by uncertainties of the treatment planning algorithms and minor positioning errors. Thus, the proposed PET method might offer a useful tool for assessing unpredictable deviations between planned and actual treatment. Moreover, PET-based verification might be beneficial for patients having metallic implants, where known shortcomings of the treatment planning algorithms in combination with artifacts of the CT-based patient model are of major dosimetric concern in ion beam therapy [18].

The participating patients are expected to benefit from this study, as in the eventuality of detected discrepancies a timely intervention could be undertaken, thus guaranteeing an improved treatment quality than without PET monitoring. Moreover, site-specific patient-population information on the ion range precision at HIT might enable in-vivo validation of the CT-range calibration curve as well as safe reduction of the treatment margins to promote enhanced treatment plan conformality for full clinical exploitation of the ballistic selectivity offered by ion beam therapy.

## Methods and Design

### Aims of the Study

The purpose of this clinical study is to investigate the clinical feasibility and effective benefit of off-line PET for quality assurance of scanned proton and carbon ion beam therapy for a large patient population.

The specific aims are to

1) Acquire PET/CT scan data on patients undergoing external beam ion therapy for a representative population of different tumour sites in order to be able to conclude which patients might in future benefit from PET/CT monitoring.

2) Analyze these data to determine the accuracy with which the beam range can be monitored and the actually delivered dose can be estimated.

3) Analyze these data (acquired during at least three fractions at the beginning, the middle and the end of the regular treatment course) to determine whether quantitative changes of the PET signal after delivery of the same treatment fraction dose can be indicators of physiological modifications connected to tumour response.

4) Assess the possibility of using PET/CT monitoring for quality assurance and adaptive strategies in scanned ion beam therapy.

### Procedure to be evaluated

The PET/CT scanner to be used is a CE-labelled medical product (Siemens Biograph mCT 40). The procedure will include acquisition of a control CT for anatomical reference as well as list-mode detection of the β^+^-activity resulting from the standard therapeutic irradiation. The CT scan is performed for patient position verification as well as monitoring of anatomical changes during the course of radiotherapy and is considered standard of care. Therefore, no trial specific CT imaging will be acquired and patients will not be exposed to additional experimental doses of ionizing radiation. The PET signal to be measured is a by-product of the therapeutic ion beam irradiation, hence no additional radioactive tracer is administered to the patient. The treatment position will be reproduced at the PET/CT scanner using the same immobilization equipment used for the therapeutic irradiation, which is compatible with standard diagnostic CT and PET imaging.

The activity levels to be expected in the study are orders of magnitude lower than in the typical operation condition of the commercial PET device, which is designed for application to nuclear medicine tracer imaging. Therefore, the PET data acquisition will be performed in one single bed position and last over 30 minutes to collect sufficient counting statistics for imaging, following the same clinical protocol reported by other investigators in previous clinical trials in USA [6,10]. After the first clinical data will be collected, the available iterative reconstruction schemes of the PET scanner will be applied and the resulting images will be compared in order to identify the optimal image reconstruction settings for optimal imaging performances at the expected low statistics levels. The so identified optimal image reconstruction settings will be applied to process all the clinical data acquired in this study.

The reconstructed PET images co-registered to the control CT (using the CE-labelled software provided by the manufacturer) will be finally analysed in comparison to the planned treatment to infer information on the correctness of the actually delivered therapeutic irradiation. An additional comparison with an expected β^+^-activity distribution will be pursued [19].

### Therapeutic and Diagnostic Modes of Action

By taking part in the MIRANDA study patients are offered the possibility to determine the applied dose more precisely, since by using the PET/CT for monitoring the activation produced by the particle beam can be visualized. The potential benefit for the future of radiotherapy is to implement PET/CT in clinical routine for dose monitoring possibly providing a useful tool for necessary corrections in treatment planning or patient positioning (adaptive particle therapy).

### Side effects and risks as well as potential additional exposures during study treatment

The β^+^-activity is induced by the therapeutic irradiation; therefore, no additional exposure of the patient is required for the PET measurements. To carry out the investigation with accurate anatomical co-registration, this study is performed using a PET/CT. The additional control CT enables the researchers to explore also anatomical modifications compared to the initial imaging data acquired for treatment planning. These control CTs are performed on a regular basis during the course of precision radiotherapy for verification of patient positioning and to monitor any anatomical changes to the tumor and to normal tissue. Therefore, these CT scans can be considered standard of care, and patients will not be exposed to any additional ionizing radiation.

This study will cause the prolongation of the selected treatment sessions, because of the time needed for the transport of the patient to the remote PET/CT scanner (about 5 min) and for the PET/CT acquisition (about 30 min). The latter is mainly determined by the required 30 minutes of PET acquisition, being the CT imaging typically completed in less than 1 min.

### Study Design

Open, mono-centric, non-randomized, prospective study to evaluate PET-CT monitoring after particle therapy for position verification, dose deposition monitoring and for the implementation of adaptive strategies for particle therapy

### Inclusion Criteria

• The patient is treated at the Heidelberger Ionenstrahl Therapiezentrum (HIT) with protons or carbon ions.

• During the radiotherapeutic treatment patient positioning and anatomy is verified using validated radiological imaging such as cone beam CT, X-ray or conventional CT (Reference-Imaging as described above).

• The patient is at least 18 years of age and is able to give informed consent.

• The patient has been informed about the aims and the content of the study.

Within the study protocol, no additional radiological imaging techniques will be performed. Therefore, the patient will not be exposed to any additional irradiation.

### Exclusion Criteria

• No informed consent to take part in the study.

• Medical reasons that impair the patients from being in the supine position for the data acquisition time, e.g. pain.

• Non-compliance of the patient.

### Study plan

A patient fulfilling the inclusion criteria will be informed about the background of this study and will be offered participation. Thereafter, an information brochure about the study will be handed out to the patient, and the patients will be instructed about the study plan and procedures. Thereafter, the patient can give informed consent. This informed consent will be documented in a written form (signature on informed consent form).

After the patient has given informed consent, patients are included into the study. The study will include procedures as follows:

a. Right after a regular treatment fraction the patient will be transferred to the PET/CT scanner located on the same floor within few meters distance from the treatment sites in the HIT building.

b. A PET/CT scan will be taken. For this examination the patient will remain fixated in the immobilization device used during treatment delivery. The average acquisition time will be in the order of 30 minutes.

The procedure will be repeated for a total of at least three treatment fractions, one being selected in the first week of treatment, one in the middle of the treatment period and one during the last week of therapy.

The study will cause prolongation of the selected treatment sessions due to the transport to the remote PET/CT scanner (about 5 min) and the PET/CT acquisition (about 30 min). All subsequent data analysis will be performed without interaction with the patient.

The data will be pseudonymized and analysed.

Concomitant treatment

No concomitant treatment is part of the study protocol.

### Criteria for withdrawal

#### Individual criteria

• Pain in supine position

• Agitated or restless patient

• Discontinuation of study participation by the patient

#### General withdrawal criteria for the study

There are no general withdrawal criteria for the study protocol

### Statistical Design

Feasibility and value of post-radiation PET imaging for verification of therapeutic ion beam delivery should be validated for different organ regions. Therefore, different analysis groups will be evaluated including tumors of the brain, skull base, head and neck region, upper gastrointestinal tract (upper GI), lower gastrointestinal tract (lower GI), prostate and pelvic region. For optimal calculations and verification, 30 patients per anatomic region will be analyzed. This amounts to a total patient number of 240 patients.

After acquisition of the data, correlation of the measured activity with the acquired CT imaging for patient position and anatomy will be performed. Additionally, correlation with the calculated dose plan within the Siemens Treatment Planning System (TPS) will be performed. Potential correction vectors consisting of positional changes will be determined based on the newly acquired activity images and the imaging that had been done for treatment planning.

Correlation of the measured activity level with the applied dose and pattern of RBE-values (relative biological effectiveness) determined during the biological treatment planning for particle therapy will be performed.

As activity and dose are known to be different physical quantities, an additional calculation of the expected β^+^-activity distribution will be pursued, provided that the computational tool used for this purpose is verified to deliver a corresponding calculation of dose distribution in agreement with the certified clinical TPS.

To assess whether the calculated dose and activity distribution are different from the measured activity corresponding to the applied dose distribution, a *t*-test as a one-sample location test can be used („is the difference different from zero").

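### The total of 240 at 30 patients per region needs eight regions, but the protocol article names seven (or six), so list, quota and total do not agree

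*Protocol article*

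**What the plan says.** The sample size is derived in Methods and Design, Statistical Design, in three steps.

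- The analysis groups are introduced as "tumors of the brain, skull base, head and neck region, upper gastrointestinal tract (upper GI), lower gastrointestinal tract (lower GI), prostate and pelvic region".
- The quota is given: "30 patients per anatomic region will be analyzed".
- The total follows in the next sentence: "This amounts to a total patient number of 240 patients".

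The Abstract (Methods/Design) repeats the total and says that allocation is equal: "A total of 240 patients will be recruited, evenly sampled among different analysis groups". Its list of sites matches the one in Statistical Design, except that it mentions the liver as part of one of the groups: "upper gastrointestinal tract including the liver, lower gastrointestinal tract, prostate and pelvic region".

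Neither place names any further group, and neither states an allowance for dropout or for unusable scans.

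**The concern.** The way the total is worded makes it the direct product of the quota and the number of regions. A reader who counts the regions and multiplies by 30 does not reach 240.

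This matters because the quota per region is the only basis given for the sample size. The article states no power, significance level, effect size or standard deviation from which 240 could be obtained another way. The purpose is also site-specific. Statistical Design wants the method validated separately for different organ regions, and the first specific aim is to learn which patients, across tumour sites, might benefit from monitoring. The number of regions and the number of patients in each are therefore central to what the study can report. As written, a reader cannot tell whether each named region is to receive 30, about 34 or 40 patients, or whether a further region of 30 is planned that the article does not name.

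**Working it through.** **Inputs**

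| Input | Value | Source |
|---|---|---|
| Quota per region | 30 | Statistical Design |
| Stated total | 240 | Statistical Design; Abstract |
| Allocation | equal across groups | Abstract |
| Named regions, first part | brain; skull base; head and neck; upper GI (4) | Statistical Design; Abstract, where upper GI takes in the liver |
| Named regions, last part | lower GI; prostate; pelvic region (3, or 2 if the last two are one group) | Statistical Design; Abstract |
| Dropout reserve | none stated | – |

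The count in the last part depends on how "lower gastrointestinal tract (lower GI), prostate and pelvic region" is read. With prostate and pelvic region as separate groups, the list has 4 + 3 = 7 regions. With the two as one group, it has 4 + 2 = 6.

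**Step 1: reproduce the stated total.** The formula implied by the text is total = 30 × number of regions. Solving for the number of regions gives 240 / 30 = 8. The stated total is exact for eight regions.

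**Step 2: apply the same formula to the named regions.**

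| Regions | 30 × regions | Shortfall from 240 | Shortfall as % of 240 | Number per region if 240 is kept |
|---|---|---|---|---|
| 8 (one not named) | 240 | 0 | 0% | 240 / 8 = 30 |
| 7 (as listed) | 210 | 30 | 30 / 240 = 12.5% | 240 / 7 = 34.3 |
| 6 (prostate and pelvic as one) | 180 | 60 | 60 / 240 = 25% | 240 / 6 = 40 |

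Measured against the recomputed total, the stated figure is higher by 30 / 210 = 14.3% for seven regions and by 60 / 180 = 33.3% for six. Seven groups also cannot be exactly equal at 240: 240 = 5 × 34 + 2 × 35.

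**Step 3: test whether a dropout reserve could explain the gap.** With inflation N / (1 − d), the loss rate needed is d = 1 − N / 240.

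- Seven regions: d = 1 − 210 / 240 = 12.5%; check: 210 / 0.875 = 240.
- Six regions: d = 1 − 180 / 240 = 25%; check: 180 / 0.75 = 240.

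Either rate would close the gap, but the article states neither.

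**The case against.** The strongest defence is that the list is not closed. Both places introduce it with the word *including*, and 240 / 30 is exactly 8, so quota and total agree with each other if one group was simply not listed. The article condenses a fuller protocol, which may hold the complete list. This stands, and it limits the conclusion: a reader might infer that the sample size itself is wrong by 30, and the article does not establish that. It does not remove the inconsistency. A list that leaves out one of eight equal groups, in both places where the design is described, does not support the total drawn from it.

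A second defence is that the liver is the eighth group. It is a possible explanation, so it would go too far to say that eight cannot be reached. But the Abstract puts the liver inside the upper GI group and Statistical Design does not mention it, so this reading is conjecture.

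A third defence is a reserve: the Abstract speaks of patients recruited, Statistical Design of patients analysed. That difference would leave room for losses, but no rate is given, and Statistical Design presents 240 as the plain product of the quota.

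Two stronger consequences are tempting and are not supported.

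- A reader might infer that regions could be defined after the results are seen. Groups are defined by tumour site, which is known before irradiation and PET, and nothing in the article points to later regrouping.
- A reader might infer that some regions would fall short of their quota. If 240 patients are sampled evenly, each region gets 30 with eight groups, about 34 with seven and 40 with six, so the target of 30 is met on every reading.

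How overlapping sites are assigned to a region is a separate operational question and has no bearing on this count.

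**Conclusion.** The point holds as an unreconciled figure. The article's only derivation of its sample size does not reproduce from the regions that it names: 210 for seven regions, 30 below the stated total, or 180 for six, 60 below. The total is correct only for eight regions, and the eighth is not identified.

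The conclusion rests on two assumptions: that the quota of 30 applies equally to every region, as both places indicate, and that no reserve is built into the total, since none is stated. Which of the three items is in error (list, quota or total) cannot be settled from the article.

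The practical effect is bounded. No power statement depends on 240, and even sampling leaves no region below 30. What is affected is the stated number of groups, the number of patients in each, and whether 30 or 60 of the planned patients belong to any named group. For such patients the article describes no added radiation or tracer. The burden is about 5 + 30 = 35 minutes per session at three or more fractions.

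**What to change.** Make the list, the quota and the total agree, in identical terms, in the Abstract and in Statistical Design. Use whichever of these matches the intended design:

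1. Name the eighth region in both lists and keep 8 × 30 = 240. If that region is the liver, take it out of the upper GI group in the Abstract.
2. Keep the named regions and restate the total as 7 × 30 = 210, or 6 × 30 = 180 if prostate and pelvic region are one group.
3. Keep 240 with fewer groups, and either restate the number per region (about 34 for seven, 40 for six) or state that 30 is the number to be analysed and give the reserve that leads to 240 (12.5% loss for seven groups, 25% for six).

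In every case, say whether prostate and pelvic region are one group or two.

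The cost is a wording correction in two places. No option needs more than the 240 patients already planned; the second needs 30 or 60 fewer. No analysis has to change.

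### The Statistical Design serves the beam-range aim with correlations and a test of an undefined difference, and no planned measure is defined as a range difference in mm

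*Protocol article*

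**What the plan says.** The Aims of the Study section sets as aim 2: "Analyze these data to determine the accuracy with which the beam range can be monitored and the actually delivered dose can be estimated". The Background asks for population-based information on how reliable the delivered range is at different tumour locations. The Discussion paragraph of the Abstract and the Background hope to use such information for the CT-range calibration curve and for margin reduction.

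The Statistical Design lists these steps:

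- Correlation of measured activity with the CT, for position and anatomy.
- Comparison with the plan: "Additionally, correlation with the calculated dose plan within the Siemens Treatment Planning System (TPS) will be performed".
- "Correlation of the measured activity level with the applied dose and pattern of RBE-values", the RBE values being those from biological treatment planning.
- "Potential correction vectors consisting of positional changes will be determined based on the newly acquired activity images" and the planning imaging.
- Because activity is not dose, "an additional calculation of the expected β^+^-activity distribution will be pursued, provided that the computational tool used for this purpose is verified" to reproduce the dose distribution of the clinical planning system.
- A one-sample t-test that can be used to ask whether calculated dose and activity differ from measured activity, with zero as the null value.

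The Abstract and the section on the procedure to be evaluated also announce a comparison with simulated or expected activity. From the comparisons, the Abstract says, "conclusions on the delivered treatment will be inferred".

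**The concern.** Aim 2 needs the size of the range error: how far, in mm, the measured fall-off lies from where it should lie, on average and in individual patients. A correlation does not give this, for three reasons.

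- It is unchanged by any error of scale.
- Two distributions that are both high in the irradiated volume and low outside it correlate strongly even when their distal edges differ by some mm.
- Against dose, the reference itself is unsuitable. The Background says so: "As activity and dose are different physical quantities, an additional comparison of the acquired PET images with a corresponding activation pattern" is strongly recommended. If the activity edge and the dose edge do not coincide under correct delivery, the coefficient need not be highest under correct delivery.

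The stake is whether the trial can report range precision by tumour site, which is the information the article hopes to carry into calibration and margins.

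**Working it through.** The article gives no coefficient, region of interest, range tolerance, SD or alpha, so there is no figure of its own to reproduce. The calculations below use assumed profiles and show what can happen, not what will be found at this centre.

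**1. Depth-profile model (assumed).** One dimension, 0.5 mm grid, spread-out Bragg peak dose. Activity ends 4 mm before the range, with a 15 mm fall-off for protons or a fragment peak near the end of range for carbon. PET blur is 7 mm FWHM, with no noise. The true range is shifted from -20 to +20 mm (positive = overshoot), and Pearson r is taken between the shifted measured activity and (a) planned dose or (b) expected activity.

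(a) Against planned dose:

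| Profile | r at correct range | Highest r | Shift at highest r |
|---|---|---|---|
| Proton, range 150 mm | 0.869 | 0.960 | +15 mm |
| Proton, range 100 mm | 0.864 | 0.970 | +10 mm |
| Carbon, range 120 mm | 0.861 | 0.882 | about -3 to -4 mm |
| Proton 150 mm, window 120 to 170 mm | 0.744 | 0.968 | +10 mm |

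In all four cases the coefficient is highest at a wrong range. The direction depends on the profile: overshoot for the proton cases, undershoot for carbon.

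(b) Against expected activity (r = 1.000 at the correct range in every case; overshoot values shown, undershoot values nearly the same):

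| Profile | 3 mm | 5 mm | 10 mm |
|---|---|---|---|
| Proton, 150 mm | 0.996 | 0.988 | 0.956 |
| Proton, 100 mm | 0.994 | 0.984 | 0.941 |
| Carbon, 120 mm | 0.963 | 0.901 | 0.678 |
| Proton 150 mm, distal window | 0.984 | 0.958 | 0.850 |

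The maximum is now in the right place. For whole proton profiles a 5 mm error costs 1 - 0.988 = 0.012 or 1 - 0.984 = 0.016. For carbon it costs 1 - 0.901 = 0.099.

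**2. Second model (assumed).** A three-dimensional block: 60 x 60 mm field, activity from 20 to 140 mm depth, 7 mm FWHM blur, region extended about 20 mm laterally and 30 mm distally. Against expected activity, r is 0.99 at 4 mm, 0.98 at 6 mm and 0.96 at 10 mm. This agrees with the whole proton profiles above.

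**3. The other planned steps, set against aim 2.**

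- *Correction vectors*: defined as positional changes, not as a difference in beam range.
- *Expected-activity calculation*: the right reference, but in the Statistical Design it is conditional, and no measure of the difference is attached to it.
- *t-test*: the quantity tested is not defined. It sets both dose and activity against measured activity, and dose has no common scale with activity. Against dose, a non-zero difference is expected even under correct delivery.

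**4. What a test against zero leaves out.** Suppose the t-test were applied to one range difference in mm per patient, with the article's 30 patients per region, two-sided alpha 0.05 (assumed) and an assumed SD. The non-centrality is (mean shift / SD) x √30; for 2 mm and SD 4 mm it is 0.5 x 5.477 = 2.74.

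| SD | Power, 2 mm mean shift | Power, 3 mm mean shift | 1.96 x SD |
|---|---|---|---|
| 2 mm | 1.00 | 1.00 | 3.9 mm |
| 4 mm | 0.75 | 0.98 | 7.8 mm |
| 6 mm | 0.42 | 0.75 | 11.8 mm |

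The last column is the half-width of the limits of agreement. With a mean difference of zero and SD 4 mm, the test would be non-significant 95% of the time, while individual differences would run from about -7.8 to +7.8 mm. The test speaks to the mean alone, and even there it does not give the size.

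**The case against.** The strongest reply is that correlation is a loose word here. The Background speaks of correlating activity with plan and anatomy in the sense of comparing images, and a coefficient between activity and CT values would say little about patient position. No coefficient, region or threshold is named. On this reading the point is an omission, and an article commonly leaves operational detail to a full protocol or analysis plan that is not shown. Part of this stands: the article does not prove that a coefficient is intended, and details such as the fall-off level or the normalisation need not appear in it. But the loose reading does not supply what aim 2 needs, because an image overlay gives no range error either. The Statistical Design does state its comparisons, and none of them is a range measure.

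A reader might infer stronger claims that the documents do not support:

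- *That correlation is the only comparison.* It is not: correction vectors, an expected-activity comparison and a t-test are also planned.
- *That a high coefficient will be taken as proof of correct delivery.* No section sets a decision rule on a coefficient. The correlation with dose and RBE concerns the activity level and is not offered as a range measure.
- *That the coefficient barely moves whatever the range error.* This fits errors of a few mm in whole proton profiles. It does not fit carbon or a distal-edge window, and the article covers both ion species.
- *That the coefficient misleads against expected activity too.* In every assumed case it peaked at the correct range.

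**Conclusion.** The point holds in this limited form: the measures named in the Statistical Design do not match aim 2. Correlation is not a measure of agreement. Against dose, which the article itself calls a different quantity from activity, it was highest at a wrong range in every assumed profile, by 3 to 15 mm. Against expected activity it was correctly placed but insensitive for whole proton profiles, with a loss of 0.012 to 0.016 at 5 mm. It was clearly more sensitive for carbon, with a loss of about 0.10. The remaining planned steps do not fill the gap, because none is defined as a range difference and a test against zero does not give the size of the error.

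The numbers rest on assumed profile shapes, ranges, edge offset and blur. The argument that association is not agreement does not depend on them. The change is worth making before analysis. The point does not say that the data to be collected are unfit for aim 2.

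**What to change.** In the Statistical Design, define the range measure as the difference in mm between the distal fall-off of measured activity and that of expected activity, per scan and per portal. One option is the 50% level along the beam direction, with each distribution normalised to its own plateau. Restrict it to beam paths whose distal edge is not overlapped by another portal. Report the mean, SD and limits of agreement per region.

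If the t-test is kept, apply it to this difference. Since each patient has at least three scans, use one value per patient or allow for the repeated values. Keep the correlations with dose and RBE as descriptive, and draw no conclusion on range from them.

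The cost is a change of wording and a small program on images and calculations already planned, with no extra scans or patients. There are two drawbacks. Portals with an overlapped distal edge drop out of the range analysis, so their number should be reported. The analysis also depends on the expected-activity tool being verified, so the article should say that aim 2 depends on that step.
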